## Abstract

**Background:**

Regular physical activity (PA) is associated with many health benefits during childhood, and tracks into desirable PA patterns and health profiles in adulthood. Interventions designed to support these behaviours among young children are critical. Family-based interventions focusing on parent-child activities together (i.e., co-activity) among preschool-aged children are warranted. Targeting parental support practices can increase the frequency of co-activity, however interventions must move beyond merely building intention and planning skills for successful maintenance. Interventions designed to increase co-activity habit strength may facilitate the sustainability and thus impact child PA. The purpose of this study is to compare the effects of three intervention conditions designed to increase child PA through co-activity: a standard *education* condition (information about benefits), a planning (action planning, coping planning) + education condition and a habit (context-dependent repetition from prompts and cues) + planning +education condition.

**Methods/design:**

A longitudinal three-arm parallel design randomized trial will compare three conditions over six months. Families are eligible if they have at least one child between 3y and 5y that is not meeting 60mins/day of moderate to vigorous physical activity (MVPA). The primary outcome (child MVPA) is assessed via accelerometry at baseline, six weeks, three months and six months (primary endpoint). Intervention materials targeting co-activity are delivered post baseline assessment, with booster sessions at six weeks and three months. Parental co-activity habit, parent-child co-activity and other behavioural constructs are also assessed via questionnaire at all measurement occasions. As tertiary outcomes, parental PA is measured via accelerometry and co-activity is measured via a Bluetooth-enabled proximity feature. A total of 106 families have been recruited thus far from the Greater Victoria region. The study is ongoing with a minimum target of 150 families and an anticipated recruitment completion date of August 2022.

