### Justification of sample size

G-Power (Version 3.1.9.2) was used to calculate sample size. With 4 repeated assessments, 3 groups, a power of .90, an alpha of .05, effect sizes ranging from .25 to .30, and an anticipated attrition rate of 15% [34], a minimum of 165 families with a goal of 240 families (i.e., 55–80 families per condition) are needed to show a significant difference in physical activity accelerometry (minutes of MVPA primary outcome) by condition over time. The effect sizes represent the findings from our prior intervention research comparing planning to education with this demographic [34] and considering our pilot study on habit formation [42], yet it is clearly in the clinically meaningful range for the detection of differences between the planning and habit formation conditions [107, 108]. However, detection is dependent on the performance of the habit versus planning conditions which is largely unknown.

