## Discussion

To date, we have obtained ethical approval, registered the trial, and have recruited 106 families from the Greater Victoria region. Ethical approval was received from the University of Victoria Human Research Ethics Board. We currently anticipate recruitment will be complete by August 2022. From the 106 parents assessed for eligibility, 94 have completed all of the baseline measures, 49 have completed the six-week measures, and 47 have completed the 3 month measures, and 44 have completed the 6 month measures and exit interview concluding the study (see Fig. 2 for Participant Flow Diagram). The study is ongoing and data collection will continue through 2021 (with the possibility of extending into 2022).

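### The abstract's minimum of 150 families contradicts the sample-size section's calculated minimum of 165, and no revised calculation supports the lower figure

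*Protocol article*

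**What the plan says.** The Methods/design part of the abstract reports progress and a target: "A total of 106 families have been recruited thus far", and "The study is ongoing with a minimum target of 150 families". It anticipates that recruitment will finish in August 2022.

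The section Justification of sample size states "a minimum of 165 families with a goal of 240 families (i.e., 55–80 families per condition) are needed". Its inputs are power .90, alpha .05, "effect sizes ranging from .25 to .30", 15% attrition and, in its words, "With 4 repeated assessments, 3 groups".

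The Discussion also calls the 106 families recruited, but then writes "From the 106 parents assessed for eligibility, 94 have completed all of the baseline measures". The sections on eligibility and procedures say that families whose child meets the activity guidelines on baseline accelerometry are excluded, and that randomisation follows this step. On timing, the Discussion repeats August 2022 for the end of recruitment and says that "data collection will continue through 2021 (with the possibility of extending into 2022". The primary endpoint is at six months.

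**The concern.** Both 150 and 165 are called a minimum for the same trial. The lower figure appears without a revised effect size, power or attrition rate. A floor matters because a team may reasonably regard recruitment as sufficient once it is reached. If recruitment ended at 150, a null result would be read against a 90% power statement that was calculated for a larger trial. The sample-size section itself concedes that the performance of habit formation relative to planning is largely unknown, so there is little margin to give away.

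Two related ambiguities affect how the target should be read. The sample-size figure is expressed per condition, so it refers to families allocated to an arm. It is not clear that the 150 does, because the 106 reported beside it carries two different labels. Separately, a family recruited in August 2022 reaches the six-month endpoint in about February 2023, which lies outside the data-collection period that the Discussion describes.

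**Working it through.** **Inputs.** From Justification of sample size: three groups, alpha .05, power .90, effect sizes .25 and .30, attrition 15%, minimum 165 (3 × 55), goal 240 (3 × 80). From the abstract: minimum target 150. The effect-size metric is not named; I read it as Cohen's f, the G*Power metric for analysis of variance. The correlation among repeated measures is not stated.

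**Step 1: reproduce the stated figures.** One-way omnibus F test: df1 = 2, df2 = N − 3, non-centrality λ = N × f².

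- f = .30: the smallest balanced N with power of at least .90 is 144 (λ = 144 × .09 = 12.96, power .901). 144 × 1.15 = 165.6, against the stated 165.
- f = .25: N = 207 (λ = 207 × .0625 = 12.94, power .902). 207 × 1.15 = 238, against the stated 240.

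So 165 goes with f = .30 and 240 with f = .25. If attrition is handled by dividing by 0.85, the results are 144/0.85 = 169.4 and 207/0.85 = 243.5, also within 3% of the stated figures.

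**Step 2: power at each minimum, after 15% attrition.**

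| Families | Completers | Power, f = .30 | Power, f = .25 |
|---|---|---|---|
| 165 | 165 × 0.85 ≈ 140 | .89 | .75 |
| 150 | 150 × 0.85 ≈ 127 | .86 | .70 |

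The difference due to 150 against 165 is about 3 points at f = .30 and about 5 at f = .25. Removing attrition by dividing by 1.15 (143.5 and 130.4 analysed) gives .90 against .87 and .76 against .72.

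**Step 3: dependence on the model.** For a repeated-measures test of the between-group factor with four assessments and correlation ρ, λ is multiplied by 4/(1 + 3ρ).

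- ρ = .5 (assumed): multiplier 1.6. Power at about 127 completers is about .97 (f = .30) and .89 (f = .25).
- ρ = .8 (assumed): multiplier 1.18. Power is about .91 and .78.

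None of the repeated-measures variants tried (between-group factor and group-by-time interaction, three or four assessments, ρ from .3 to .8) yields both 165 and 240. At ρ = .5 with four assessments, for example, the between-group test needs 93 and 132 before attrition, and the interaction test needs 27 and 39.

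**Step 4: counting stage, as an illustration only.** Suppose the 150 is counted like the 106, and the 94/106 fraction with complete baseline measures is a permanent loss. Both are assumptions. Then 150 × 94/106 = 133 families and 133 × 0.85 = 113 completers, with power about .81 (f = .30) or .65 (f = .25). If there is no such loss, the figures are those of Step 2.

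**Step 5: calendar.** August 2022 + 6 months = February 2023. The Discussion's latest stated possibility is 2022.

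**The case against.** The strongest reply is that the power consequence is modest and uncertain. On the reproducing calculation 165 families already give only .89 at f = .30 and .75 at f = .25, so most of the gap between .70 and .90 at the smaller effect is present at 165 too. The planned analysis is a hierarchical linear model over four assessments, and a repeated-measures test with a correlation of .5 would keep 150 families above .90 at f = .30. Both points stand. They limit the size of the problem but do not explain the 150, because no repeated-measures variant tried produces the protocol's own 165 and 240. The text also offers no such argument for the lower figure.

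The 150 is also a minimum target and not a stopping rule, and the sample-size section keeps a goal of 240. That is fair: the trial may recruit more. It still leaves two different floors.

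A reader might infer three stronger things that the documents do not support:

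- **That the 150 is counted before screening.** No text states its counting stage. The Discussion uses both labels for the 106, telephone screening comes before the baseline visit, and recruitment is rolling, so the 12 families without complete baseline measures may be pending. The flow diagram is not available in the text reviewed and may clarify this. Any rate of exclusion by accelerometry would be invented.
- **That 90% power is definitely not delivered.** This depends on a model and a correlation that are not given.
- **That families recruited late would have no primary endpoint.** The six-month assessment has no calendar cut-off, and both dates are worded as expectations.

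**Conclusion.** The contradiction holds as written: the abstract's minimum is 15 families below the minimum that the protocol's own calculation requires, and no recalculation is given. Under the one-way F test that approximately reproduces the stated figures, with f as the metric and 15% attrition, power at 150 is about .86 (f = .30) or .70 (f = .25). At 165 it is about .89 or .75. The cost attributable to the discrepancy is therefore about 3 to 5 points, and the absolute values would change under another model.

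The counting stage of the 150 is unclear and should be stated, but any further loss of power from it is an assumption. The calendar statements are inconsistent and need reconciling; they do not show that endpoint data will be lost.

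**What to change.** - State one minimum in the abstract and in Justification of sample size, counted as randomised families.
- Either use the calculated 165, noting that full power of .90 at f = .30 after 15% loss needs 144/0.85 ≈ 170, or keep 150 and restate the power as about .86 (f = .30) and .70 (f = .25). In both cases name the test, the effect-size metric and, if a repeated-measures calculation is meant, the assumed correlation.
- Use one label for the 106 and say at which stage they are counted: assessed, baseline complete or randomised. If the flow diagram already shows this, make the abstract and Discussion agree with it.
- Word the data-collection period so that it runs until the last randomised family has completed its six-month assessment.

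The cost is wording in the protocol, and in the registration if it carries these figures. If 150 is kept, the stated power becomes less favourable. If 165 or 170 is adopted, the recruitment floor rises by 15 or 20 families.

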**Discussion:**

This protocol describes the implementation of a randomized trial evaluating the effectiveness of a *habit formation* group compared with a *planning* group and an *education* only group to increase child PA through targeting parent-child co-activity. This information could prove useful in informing public health initiatives to promote PA among families with preschool-aged children.

**Trial registration:**

This trial was prospectively registered on clinicaltrials.gov in February 2016, identifier NCT03055871.

## Background

Regular physical activity (PA) is associated with a 20–30% risk reduction for over 25 chronic conditions [1]. Unfortunately, many Canadian adults and children do not meet recommended guidelines to optimize these benefits [2, 3]. The antecedents of health risk factors begin in early life, making primary prevention efforts in childhood of paramount importance [4]. To this end, although disease and health complications typically present in adulthood, there is convincing evidence to suggest regular PA among children protects against many negative physical, psychological, social, and cognitive health outcomes [5–8]. Effective interventions aimed at helping preschool-aged children develop PA patterns are critical for long-term population health. Designing such interventions requires an understanding of factors that influence PA of preschool-aged children.

Developing PA practices before formal schooling may be optimal for cementing health behaviours to be carried through the school years and ultimately establishing a pattern for PA over the life-course [9]. Thus, the home is one important environment to target and there remains a need to promote PA within the family unit. Preschool-aged children aged three to 5 years spend considerable time in the care of their parents. Indeed, parents appear to be the ‘gatekeepers’ of PA during family time [10, 11]. Unsurprisingly, parental influence on PA has received considerable research attention [12] and a review of family-based interventions found parent support to be a consistent determinant of child PA [13]. One type of parental support is co-participation, whereby parents facilitate activities in which they can be active with their children. Co-activity is defined herein as any energetic activity that gets parent and child moving together, through which the child is active at a moderate or vigorous intensity. Co-activity has been identified as a crucial factor in the support of PA for preschool-aged children [14]. A recent national survey examining parental beliefs on co-activity found that early childhood was considered the optimal time for co-activity practice [15]. This type of support has numerous advantages: it models an active lifestyle [16], fosters healthy family dynamics though bonding [17], and helps get parents active, a demographic plagued by lower PA rates compared to comparable age-matched adults without children [18, 19].

Intervention research targeting parent-child co-activity has shown positive effects [20, 21], which highlights the promise of family-based intervention. However, this is balanced by several reviews indicating interventions targeting parent-child co-activity have largely lacked success [22–25]. This underscores a clear need to continue to hone theory behind parent-child co-activity to facilitate reliable success. The reason for these negligible findings may be because the dominant approach is educating parents on the benefits of PA [13], which does not appear to be a driver for behaviour change, likely because the benefits of PA are already well-recognized among parents [14, 26–29]. Furthermore, a recent study suggests that most parents have positive intentions to support child PA, yet few follow through on enacting this support [30]. Clearly, existing intervention targets for parental support have not been effective at bridging the intention-behaviour gap. Taken together, there is a need to focus on how intentions to support child PA (specifically through parent-child co-activity) can be translated into behaviour and sustained over the long term.

In order to bridge the intention-behaviour gap to support child PA through co-activity and foster behavioural follow through, theoretical approaches for behaviour change that move beyond intentional constructs are needed. Several alternate models propose that self-regulation strategies such as planning are integral (e.g., [31–33]). This type of approach has been applied to family-based interventions and has shown success in the short term [13]. However, planning may be difficult for parents to sustain over time, risking a failure to maintain parental support of child PA. As an example, a recent study comparing a family-based planning condition to an education only control condition found significantly increased child PA at 6 weeks but the effect waned over time, suggesting additional strategies are needed for PA maintenance [34]. Of particular importance, the process evaluation of this study indicated that several parents rejected the planning approach, citing that it was exhausting unto itself and thus unsustainable.

One approach that may assist in converting intentions into lasting parental support (in the form of parent-child co-activity) is the Multi-Process Action Control (M-PAC) framework [35, 36]. M-PAC proposes that self-regulatory tactics, such as planning, assist with the translation of intentions during the adoption of a behaviour, but maintenance is determined, in part, by reflexive components such as habit. This approach suggests that developing habits over time can reduce the need for conscious motivation and self-regulation, thereby facilitating sustained behaviour. Habits operate through stimulus-response bonds which automatically instigate a behaviour [37], and are thought to contribute to physical activity through repeated consistency in behavioural practices, salient cues linked to initiation, and affectively rewarding behaviour [38–40]. Extant research in the PA domain indicates interventions designed to promote habit strength through prompts, cues, context-dependent repetition and consistent practice may have promise in promoting PA [37, 41–44], likely because habits contribute to PA maintenance somewhat separately from intention (or goals) [41, 45]. Indeed, a recent study applying M-PAC to parental support for child PA found habit to be the largest independent correlate of behavioural follow-through [30], indicating that interventions that promote habit strength are warranted.

### Study objectives and hypotheses

The primary objective of this study is to investigate the effects of a theory-based intervention targeting parent-child co-activity to promote child MVPA (primary outcome) across 6 months. Namely, the effect of a *habit formation* (context-dependent repetition from prompts and cues, consistent practice) and planning and education condition (action planning, coping planning, and information on benefits), will be compared against a *planning* and education condition (action planning, coping planning and information on benefits) and a standard *education* condition (information on benefits) on child PA. Consistent with previous research [30, 46], it is hypothesized that the habit formation intervention targeting parent-child co-activity will yield greater increases in co-activity and subsequently influence objectively measured child MVPA at 6 months (primary end-point) compared to those in the planning and education conditions. Further, based on extant research on the efficacy of planning interventions among families [34], we predict that children in the planning condition will show greater increases in MVPA compared to the education-only group because planning aids PA adoption, however these initially efficacious effects will wane over time due exhausting nature of constant volitional planning and the lack of strategies to assist with maintenance.

The secondary objective will be to explore group differences among behavioural outcomes using a mediation model. We hypothesize that child PA will be influenced by parent-child co-activity, which will be a result of PA support from parents in the form of co-participation. Higher PA support (co-participation) is expected to come from those in the habit formation condition, followed by self-regulatory planning compared to education. Thus, it is hypothesized that the covariance of the assigned condition (habit formation, planning, and education) will be explained by parental co-activity habit strength through the use of context repetition/cues and consistency/repeated action (i.e., manipulation check).

Tertiary objectives include evaluating both self-reported and objectively measured physical activity for parents as well as parent-child co-activity (via accelerometry using a Bluetooth enabled proximity tagging feature). It is hypothesized that parents in the habit formation condition will show higher light and moderate intensity PA compared to the other conditions due to consistent performance of co-activity with their children.

Additional parental factors such as quality of life, parental competence, and family functioning will also be examined. We hypothesize that conditions that increase PA will show commensurate increases in these factors. Finally, exploratory analyses will focus on seasonal, or gender differences across primary outcomes by assigned condition [47, 48].

## Methods

This study is approved by the University of Victoria Human Research Ethics Board (HREB), reference number BC16–231. The reporting of the trial follows the Standard Protocol Items: Recommendations for Interventional Trials (SPIRIT) guidelines [49] and will harmonize with the Consolidated Standards of Reporting Trials (CONSORT) guidelines [50]. For SPIRIT information, a diagram is included (see Fig. 1). The trial was prospectively registered with the Clinical Trials Registry maintained by the National Library of Medicine at the National Institutes of Health (ClinicalTrials.gov) Trial ID NCT03055871.

**Fig. 1 Fig1:**
[figure not shown]
SPIRIT 2013 Schedule of enrolment, interventions, and assessments

### Design

This study is a randomized trial with a single-blinded, three-arm parallel design. Upon the completion of baseline measures (questionnaire, accelerometer wear) participants are assigned to one of three groups: 1) standard co-activity education (education condition); 2) co-activity education and planning (planning condition); 3) co-activity education, planning, and habit formation (habit formation condition). The main outcome measure of child MVPA (dependent variable) will be assessed at the primary end point of the trial (6 months) with secondary assessments time points at 6 weeks and 3 months.

### Participants and eligibility

To be considered eligible, families must reside in the greater Victoria region, in British Columbia, Canada. Both single and common-law/married adults are eligible so long as they have at least one child between ages of three and 5 years. This age range was informed by a literature review [51] and survey data suggesting that children aged 5 years or younger engage in sporadic PA that is not amenable to formal sport programs and thus parent-facilitated co-activity is critical. Age range was also delimited on pragmatic grounds: school-aged children often start structured PA/sport and engage in peer play which does not lend itself to parent-facilitated co-activity. In cases where more than one child is eligible, a target child will be randomly chosen but all willing children will be included in the study. It is required that families are safe to engage in moderate intensity physical activity (assessed via the Get Active Questionnaire [52]. Those individuals who are not able to participate in moderate intensity physical activity will be excluded for safety reasons. Finally, families are only included if parent-declared child PA is less than recommended by the Canadian 24 Hour Movement Guidelines [53]. Because inactive children are the true target of such an intervention, it is important to delimit participants to children not meeting PA guidelines and it follows families are also screened via baseline accelerometry results as a secondary assurance. Families with designated children who meet the Canadian guidelines are subsequently excluded from the trial. Target parent(s) PA is not an eligibility criterion because increases in parent PA is not a primary outcome.

